## F. Study Type

This is a hypothesis-generating descriptive study that uses both cross-sectional and cohort designs.

## G. Study Design

**Research Aim A)** We will use a cross-sectional design. For this analysis, we will include data from all active 'acceptable patients' ( $\geq 16$  years of age) who were permanently registered to English General Practices between 1 January 2010 and 31st December 2020. The practices included will be those contributing with 'Up to standard' data during the study timeframe.

**Research Aims B and C)** We will use an observational cohort design. Considering that this is a hypothesis-generating study, our main aim is not to compare exposed and unexposed groups of patients, instead, we will evaluate the development of multimorbidity clusters to generate hypotheses on their trajectory and to help identify homogeneous groups of patients who may share similar prognosis and health care needs. We will assess these trajectories throughout the follow-up period and look at the potential factors that affect them, including where specific life course events occur, and in the context of specific prescribing patterns (particularly polypharmacy). The outcomes of this analysis will be the development of multimorbidity clusters of diseases through the years, polypharmacy and mortality. We will censor the patients who have transferred out of their practice during the follow-up period.

## H. Feasibility counts

We will include all people registered with a GP included in CPRD who meet inclusion criteria (see Definition of the Study Population) irrespective of whether they have multimorbidity or not. This will allow us to define multimorbidity using new criteria, and to determine its onset longitudinally. We have determined feasibility of our approach using a recently published study on multimorbidity by Cassel et al., 27.2% of the eligible CPRD population ( $n = 403,985$ ) were identified as having two or more conditions on 1 January 2012. Our proposal will adopt similar criteria to select our study's population, i.e. in defining 'acceptable patients' and 'up to standard' data. In a cohort size of patients eligible for linkage using CPRD GOLD ( $n = 9,209,834$ ) and considering a multimorbidity prevalence of 27.2% we anticipate identifying at least 2,505,075 patients with two or more conditions. Given the importance of understanding ethnic variation in multimorbidity, we have used Office for National Statistics ethnicity data to predict that of the 9,209,834 people in CPRD GOLD (assuming a representative population), approximately 700,000 will be people of Asian/Asian British ethnicity, and 300,000 will be people of Black/African/Caribbean/Black British ethnicities.

For CPRD Aurum data, in the estimated cohort size of 35,443,993 patients eligible for linkage, we expect to identify around 9,640,766 patients with two or more conditions considering the same prevalence of multimorbidity identified by Cassel et al. (8) (27.2%). Assuming the representativity of CPRD Aurum data, and applying the prevalence of 7.8% and 3.5% of Asian/Asian British and Black/African/Caribbean/Black British ethnicities, we would have approximately 2,700,00 and 1,200,000 people of those respective ethnicities. However, we will select only the population of East London from Aurum dataset (please see section K. Definition of the Study Population) as these will form a validation set from an ethnically-diverse population.

It is important to highlight that the Cassel et al study population size provides a rough estimate of the expected number of patients available in CPRD with linked data set. However, by comparison to Cassel et al, we will include a longer timeframe (2010 to 2020), younger population (from 16 years old, rather than 18 years old) and a broader set of long-term conditions (220 rather than 36), thereby increasing our population size.

## I. Sample size considerations

[figure not shown]

To estimate the minimum sample size necessary to meet our research aims, we have based our parameters in the prevalence of multimorbidity ( $\geq 2$  conditions) of 27.2% found in the study of Cassel and colleagues (8). As this is an observational study, the sample size calculation was obtained using the following formula (13):

$$n = \frac{Z^2 P(1 - P)}{d^2}$$

In this formula,  $n$  is the sample size and  $Z$  is the test statistic corresponding to 95% confidence level ( $Z = 1.96$ ). The significance level was set at 5% ( $p=0.05$ ).  $P$  is the expected prevalence of multimorbidity which we set to 27.2%.  $d$  is the precision of the estimate, corresponding to the margin of error in the prevalence of multimorbidity given by its confidence intervals from the Cassel study. We set the  $d$  to be 0.20%.

$$n = \frac{1.96^2 \cdot 0.272 \cdot (1 - 0.272)}{0.002^2}$$

$$n = 190,174$$

$$Z = 1.96$$

$$P = 27.2\% = 0.272$$

$$1-P = 0.728$$

$$d = 0.2\% = 0.002$$

Using the numbers given above, to identify the prevalence of multimorbidity among our population, minimum 190,174 subjects are required. Considering there is a possibility of 10% missing data, 209,191 subjects would be required.

Nevertheless, it is important to consider that Cassel' study included a list of only 36 conditions, and presented a higher prevalence of multimorbidity compared to previous studies on multimorbidity (5,14). If we were planning to replicate known common comorbidities, then the given sample size would be sufficient. However, we aim to generate new clusters using a data driven approach (which has a better performance with large amount of data) that incorporates lower prevalence diseases and more than 200 conditions. Therefore, assuming the inclusion of lower prevalence conditions, such as HIV (prevalence = 0.09%), we expect to need a larger sample size to build robust clusters that include these and that also allow us to investigate variation by ethnicity.

We are strongly guided by recent work undertaken by the CALIBER team (University College) who have undertaken a rigorous study of age-based trajectories of disease clusters (using nearly 300 conditions) using CPRD data (2,15). In this study, it was feasible to build data-driven disease clusters across 3 million people included in CPRD.

According to the release note of CPRD GOLD and Aurum database published in February 2021, there are a total of 9,209,834 and 35,443,993 patients eligible for linkage in those respective databases. Considering our study population definition (e.g. 'up to standard' data and 'acceptable patients') and design, we expect that our study will be sufficiently powered using the data of approximately 3 million acceptable patients from GOLD. We propose using GOLD as our primary dataset. Using the same study population definitions, we anticipate there being 11 million acceptable patients in the Aurum database. However, we will use Aurum as a secondary validation dataset limited to the ethnically-diverse East London population, which includes seven Clinical Commissioning Groups (Tower Hamlets, City and Hackney, Newham, Waltham Forest, Barking and Dagenham, Redbridge and Havering), being a smaller dataset required, according to the CPRD collected-data from those practices.

#### J. Planned use of linked data (if applicable):

This study will use individual level anonymised data within linked primary and secondary care records. The use of linked data from the NHS Hospital Episode Statistics (HES) for admitted-patient care will allow us to identify hospital-

[figure not shown]

coded conditions that contribute to multimorbidity, to characterise pregnancies, and to add information on health service utilisation, such as number of hospital admissions per year, and to obtain a higher completeness of ethnicity data (a core variable to our study). Moreover, the use of HES data will enable us to undertake validation of diagnosis across primary and secondary care (e.g. HIV and cancer). The linkage to the Office for National Statistics Death registries will allow us to know the cause of death and therefore understand the most common cause of death according to the patterns of diseases' clusters.

Linked area-based measures of deprivation will include the Indices of Multiple Deprivation (IMD) for both patient and practice level. The IMD is an estimate of socioeconomic status that play an important role to multimorbidity. We will use patient level IMD where available. For patients without linked patient level IMD, we will use practice level IMD as a proxy.

We expect that the identification of specific multimorbidity clusters and their different trajectories across ethnic groups will help identify groups of patients who may share similar prognosis and health care needs. Our study findings will support clinicians in the stratification of clinical care and will contribute to preventive strategies across multimorbid conditions. We expect that our study outputs may help improve patient care either directly, e.g. by recognising a common cluster of multimorbidity linked to a specific disease, or indirectly providing scientific support to the inclusion of multimorbidity in clinical practice guidelines and public health policies.

#### K. Definition of the Study population

Our study population comprises all acceptable patients permanently registered in any English General Practice that meet 'up to standard' CPRD GOLD data quality criteria between January 1, 2010 and December 31, 2020 and who ever had a recorded multimorbidity condition during this time frame. Patients are labelled as 'acceptable' if they meet acceptable data quality criteria for use in research.

With regards to the observational cohort design, our cohort will include all individuals aged 16 and over contributing data between January 1, 2010 and January 1, 2021. Each patient will have their Index Date, when the presence of multimorbidity will be defined. All included participants will be required to have 1 year of registration before the Index Date to maximise the record of prevalent cases across at least 12 months of registration. The patients will be followed from their Index Date until the earliest of dying, leaving the CPRD database, or the end of the follow-up period (1st Jan 2021).

We will use the CPRD Aurum as a validation data set, aiming to replicate our methods and validate our findings using the East London population, which comprises seven Clinical Commissioning Groups (Tower Hamlets, City and Hackney, Newham, Waltham Forest, Barking and Dagenham, Redbridge and Havering). The population specifications for Aurum will follow the same specifications as GOLD, i.e. in defining 'acceptable patients'. Considering that there is duplicate historical data for practices that have contributed data for both CPRD GOLD and Aurum, we expect CPRD to provide a bridging file to identify the overlapping practices and dates.

Our study population will be limited to those who are eligible for linkage.

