## PART 2: PROTOCOL INFORMATION

### Applicants must complete all sections

#### A. Lay Summary (Max. 250 words)

Multimorbidity describes the situation where an individual is affected by 2 or more health conditions. Studies have shown that multimorbidity is becoming more common, and the National Health Service does not currently have services designed to tackle it well. People living with multimorbidity often need to take multiple medications and require regular contact with health services. Recent research has shown that multimorbidity exists in 'clusters', with groups of common conditions (e.g. type 2 diabetes, chronic pain, and depression) often co-existing.

Using the health records of several million people held by CPRD, we will explore unanswered questions relating to multimorbidity. Our research will focus on using novel statistical and computer science techniques to look for clusters and patterns in this health record data. We will examine these clusters and patterns of multimorbidity to better understand how they affect particular people (e.g. people prescribed specific or multiple medications, or people living with specific conditions such as cancers and human immunodeficiency virus (HIV)) and populations (e.g. people from different ethnic groups). Our approach, in combination with using historic data available from CPRD, will also allow us to uncover how and why multimorbidity develops over time, and if it is associated with early death.

We expect that the impact of our research will be wide-ranging, including supporting improvements in health and social care for multimorbidity and perhaps more efficient use of limited NHS funds.

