#### C. Outcomes to be Measured

**Primary outcome(s):**

[figure not shown]

- (a) The clusters of multimorbidity\*; and,
- (b) The multimorbidity cluster trajectories throughout the follow up period.

\*Multimorbidity will be defined as the presence of two or more long-term conditions (out of the clinical consensus-derived 220 conditions described in appendix 1) within the same individual. Unsupervised machine learning algorithms applied to the dataset will then derive and define clusters of multimorbidity, by grouping similar entities together (using an understanding of difference in distance between data points). A sample of code sets used to select conditions are shown in Appendix 2.

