### P. Plans for addressing missing data

We will assume that the individuals who do not have any recorded code do not have the disease (for further discussion, please also see Section T. Limitations on the study design). We will include patients who have complete data for the stratification variables (e.g. sex, age and ethnic groups) and who have linked measures of deprivation. Given the high levels of missingness for some covariates, i.e. body mass index, total cholesterol, and alcohol intake specific statistical techniques will be applied to handle missing-not-at-random data, e.g. sensitivity analysis and multiple imputation techniques where appropriate.

The design of the study assumes that patients who do not meet the criteria according to the coding algorithm do not have the disease. This may introduce biases due to under-reporting or misreporting. Please see section O for further details.

In the main analyses, where patients will be stratified by age and sex, any individuals with missing data for either will be excluded. In addition, patients without data for ethnicity and deprivation will be excluded from sensitivity analyses.

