## T. Limitations of the study design, data sources, and analytic methods

There are a few limitations to our study design, analytic methods and use of data sources:

- Adding only 'acceptable patients' could potentially introduce a selection bias to our study. Acceptable patients might underrepresent a group of patients that are difficult to engage, e.g. those who may often change GP practice but who are also multimorbid, and who might be from minority ethnic groups. Similarly, including only 'up to standard' data will assure high quality data, but could introduce selection bias by including general practices with better quality of, and access to, healthcare and access to primary healthcare. However, including only 'up to standard' data from acceptable patients will ensure high quality data, an essential aspect to work both with longitudinal analysis. This limitation will be addressed in our study discussion.
- The cluster analysis is dependent on the measures (e.g. variables/conditions) used to characterise the objects (e.g. individuals). Despite our comprehensive list of conditions (we will expand on the existing ~40 conditions commonly used in most of the UK's multimorbidity studies due to its data quality (mostly incentivised via QOF) to include a larger set of clinically-relevant conditions (n = 220)) our clustering solution might not be generalised as it is dependent upon the included conditions (e.g. the addition or exclusion of variables/conditions influences the clustering solution we get from the analysis). However, it will cover a broader set of conditions, compared to various studies on multimorbidity. We are aware that recording of non-incentivised conditions will be less comprehensive and therefore this may introduce bias from coding frequency/accuracy.
- We have included a few sexually transmitted conditions in our study (e.g. HIV, chronic hepatitis) that might be under-reported in the CPRD linked dataset for reasons of confidentiality, also given that in the UK, most consultations involving sexually transmitted infections are diagnosed and treated at sexual health service centres (2).
- Our study might be subject to misclassification due to unrecorded, miscoded and undiagnosed diseases. Likewise, a patient with no disease diagnoses record will be considered as disease free, even though the lack

[figure not shown]

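### Section K admits patients only if a listed condition was recorded in 2010-2020, so entry depends on re-coding, and the protocol never says whether pre-2010 codes count

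*Protocol*

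**What the plan says.** Section K (Definition of the Study population) describes acceptable patients permanently registered in English practices "between January 1, 2010 and December 31, 2020" and adds a further condition for entry: patients "who ever had a recorded multimorbidity condition during this time frame". For the cohort part, Section K also requires "1 year of registration before the Index Date to maximise the record of prevalent cases across at least 12 months of registration".

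Other sections bear on the same point:

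- Section G (Study Design), Aim A, uses the 2010-2020 dates to qualify registration. It attaches no date to the diagnosis code.
- Section H (Feasibility counts) says that everyone meeting the criteria is included whether or not they are multimorbid, so that onset can be determined over time.
- Section C (Outcomes): "Multimorbidity will be defined as the presence of two or more long-term conditions", from a list of 220, with no date window.
- Section P (missing data): "We will assume that the individuals who do not have any recorded code do not have the disease". Again no date limit.
- Section A (Lay Summary) describes the approach as working "in combination with using historic data available from CPRD", without giving a period.

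No section sets a look-back, and none says expressly that a code before 2010 counts.

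**The concern.** The 220 conditions are long-term. A diagnosis made in 2004 is still present in 2012, but it need not be coded again. Section K uses one calendar window for two purposes: when the patient must be registered, and when a condition must be recorded. The study needs only the first. The second selects patients by how often their conditions are re-coded, which is a feature of record-keeping and not of disease.

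Two things are at stake. First, patients whose only codes pre-date 2010 would be missing from the population in which clusters are formed. Combinations of seldom re-coded conditions would be thinned relative to combinations that include a frequently coded one. Second, because no look-back is stated, an analyst could carry the same window into ascertainment. Rarely re-coded conditions would then be under-counted, most of all at the earliest time point, and an old condition re-coded later could look newly acquired in Aim B.

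Timing matters. Section 11 (Data Access Arrangements) says that CPRD will extract a study-specific dataset. If Section K defines that extract, patients left out cannot be recovered by a later analysis plan.

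**Working it through.** **Plan's own figures.** No figure in the protocol measures this effect. The one calculated sample size (Section I) reproduces: 1.96² × 0.272 × 0.728 / 0.002² = 190,174.6, against 190,174 stated. It does not depend on this point.

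**Step 1: the passages side by side.** Take a patient registered from 2010 to 2020 whose two listed conditions were coded in 2004 and 2006 and never again.

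- Section K, literally: not in the population, because nothing was recorded in the window.
- Section G, Aim A: included, because registration falls within the dates.
- Section H: included, since multimorbidity status is not meant to decide entry.
- Sections C and P: multimorbid, since two conditions are present and each has a recorded code.

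The sections therefore do not give one answer for this patient.

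**Step 2: how entry would depend on re-coding.** Inputs: p is the yearly probability that an existing condition is coded again in any source; k is years of registration in the window; m is the number of pre-2010 conditions. All values of p are assumptions. Years and conditions are taken as independent, with no newly diagnosed condition in the window. The probability of exclusion is (1 − p)^(m × k).

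| p | m = 1, k = 5 | m = 1, k = 11 | m = 2, k = 11 |
|---|---|---|---|
| 0.05 | 0.774 | 0.569 | 0.324 |
| 0.20 | 0.328 | 0.086 | 0.007 |
| 0.70 | 0.002 | about 0 | about 0 |

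A patient with one condition at p = 0.05 and one at p = 0.70 over 11 years is excluded with probability 0.95^11 × 0.30^11, which is about 0. Two seldom re-coded conditions give 0.324. That contrast is the selection effect.

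**Step 3: from pre-2010 cases to all cases.** Let s be the share of cases first coded before 2010. The protocol does not give it, so take 30% to 70% as an assumed range. For patients with a single condition and k = 11, the share lost is s × (1 − p)^11:

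- p = 0.05: 0.3 × 0.569 = 17% to 0.7 × 0.569 = 40%
- p = 0.20: 0.3 × 0.086 = 3% to 0.7 × 0.086 = 6%
- p = 0.70: about 0%

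**Step 4: only if the window were also applied to ascertainment.** Section N gives January 2011, January 2016 and December 2020 as example time points, about 1, 6 and 11 years into the window. For a patient who is in the population through another condition, the probability that a pre-2010 condition is still unseen is (1 − p)^k:

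| p | Jan 2011 | Jan 2016 | Dec 2020 |
|---|---|---|---|
| 0.05 | 0.95 | 0.735 | 0.569 |
| 0.20 | 0.80 | 0.262 | 0.086 |
| 0.70 | 0.30 | 0.001 | about 0 |

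The drop between two columns is the probability that an old condition appears as newly acquired. From 2011 to 2016 it is 0.95 − 0.735 = 0.215, 0.80 − 0.262 = 0.538 and 0.30 − 0.001 = 0.299. Under-counting is worst for the least re-coded conditions. In this illustration, false acquisition is largest at the intermediate rate.

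**The case against.** The strongest reply is that the quoted words complete a description of who is in the study population. They are an entry criterion and not a rule on which of an included patient's codes count. That is correct. A reader might infer that a long-term condition counts only if recorded in 2010-2020 and is otherwise treated as absent. The protocol does not say so. Section P makes a disease absent only where there is no recorded code at all, Section C sets no window, the year of prior registration is there to capture prevalent cases, and the lay summary speaks of historic data.

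A reader might also infer that the loss falls hardest on non-incentivised conditions. Section T concedes that "recording of non-incentivised conditions will be less comprehensive and therefore this may introduce bias from coding frequency/accuracy", but it speaks of recording in general and not of a date window. The protocol has no data on re-coding by condition. It also does not define onset as the first code within the window, so reversed order in Aim B is a possibility and not a stated rule. Linked HES (Section J) may supply in-window codes for some conditions and so reduce any loss.

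Two further replies carry less weight. Section H refers to Section K for its criteria, so it could be read as subordinate. But its stated purpose, to find onset over time in people with and without multimorbidity, is not served by K's restriction. And a condition-level look-back could be left to an analysis plan that is not shown. That answers the silence on look-back, but not a criterion that the protocol itself states and that may shape the extract.

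**Conclusion.** The point holds as a defect in a stated entry rule. Followed literally, Section K drops registered patients whose listed conditions were coded only before 2010, and this disagrees with Sections G and H. The protocol neither excludes nor admits the pre-2010 codes of patients who do enter, so ascertainment is ambiguous but not shown to be wrong.

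The direction follows from the rule: the less often a condition is re-coded, the more its carriers are lost. The size cannot be derived from the document. The illustration runs from about 0 to 0.57 for a single pre-2010 condition over 11 years of registration, and rests wholly on assumed, constant and independent re-coding probabilities of 0.70 down to 0.05. The January 2011 problem and the false acquisitions arise only if the window is also used for ascertainment.

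**What to change.** In Section K:

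- Use 1 January 2010 to 31 December 2020 for registration and follow-up only, and strike the time restriction from the condition criterion.
- State that condition status at each index or assessment date uses any primary-care or linked HES code on or before that date, with the earliest code as the onset date. The deletion alone changes who enters; this sentence is what settles ascertainment.
- Reconcile the entry criterion with Section H, so that it is clear whether people without a listed condition are in the population.

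Before extraction, confirm that neither the CPRD nor the HES data are truncated at 2010.

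The cost is a few sentences and one check of the extract specification. The downside is that older records are less standardised. A sensitivity analysis limited to codes made after registration would show how much that matters. If full-history ascertainment is already intended, the edit only makes Section K say so.

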## N. Data/ Statistical Analysis

### Research Aim A)

We will estimate the prevalence of each condition included in our consensus-built list of 220 conditions across sex, age groups and ethnic groups (White, Black African and Caribbean, and south Asian). We will also describe the presence of multimorbidity ( $\geq 2$  conditions) across different sociodemographic characteristics (age, sex, ethnic groups and deprivation level).

We intend to apply unsupervised machine learning techniques to identify clusters of multimorbidity across an unselected population, and within specific ethnic groups. Recent research suggests that unsupervised learning techniques have potential to identify novel patterns and relationships from electronic health records and reveal latent disease clusters and patient subgroups (16). We will potentially use the overlapping technique, which allows each disease to belong to two or more clusters that present separate degrees of membership. The advantage of using this type of clustering is that the diseases on the boundaries between several clusters are not forced to fully belong to a single cluster, but rather are assigned membership degrees between 0 and 1 indicating their partial membership (17,18). We may apply a prevalence-based revision of the conditions included in our multimorbidity clusters (as used by Kuan and colleagues (2) who set a prevalence cut off of 0.01% in their data-driven analysis) if there is concern that very low prevalence conditions are subject to reporting bias or poor data quality.

We will describe the patterns of multimorbidity by calculating the frequencies and percentages of conditions within each cluster, and diseases will be assigned to the cluster in which they present the highest membership value. The membership value will be estimated using the ratio between the disease prevalence within the cluster by the disease prevalence in the overall population (19). We will examine how clustering varies in the context of more prevalent conditions (e.g. diabetes, hypertension, depression) compared to less prevalent conditions (e.g. HIV and cancer).

We will use the CPRD Aurum as a validation data set, aiming to replicate our methods and validate our findings in an ethnically-diverse East London population.

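### Section K's first sentence admits only people with a recorded listed condition, contradicting Sections G, N, T and its own cohort paragraph; if it governs the extract, Aim A prevalences are inflated

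*Protocol*

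**What the plan says.** Section K opens by defining the study population as acceptable patients in up-to-standard English practices between 2010 and 2020 "who ever had a recorded multimorbidity condition during this time frame". Section M uses the same term for the individual conditions that have code sets, so the natural reading is at least one listed condition. Taken literally, anyone with none is outside the study.

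Other parts of the Protocol set no such limit:

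- Section G, Aim A: "we will include data from all active 'acceptable patients", aged 16 or over.
- Section K, cohort paragraph: "our cohort will include all individuals aged 16 and over contributing data between January 1, 2010 and January 1, 2021".
- Section N, Aim A: the intention is to "identify clusters of multimorbidity across an unselected population, and within specific ethnic groups". The membership value there divides by each disease's prevalence in the population as a whole.
- Sections P and T: a person without a diagnosis code is taken not to have the disease.

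Section H includes registered people "who meet inclusion criteria (see Definition of the Study Population) irrespective of whether they have multimorbidity or not" and gives the reason: "This will allow us to define multimorbidity using new criteria, and to determine its onset longitudinally". The size figures in Sections H and I carry no condition requirement either: 27.2% is a prevalence in the eligible population of the cited study, and the 3 million expected from GOLD are described only as acceptable patients.

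**The concern.** Section K is the formal definition of the population, and Section H points to it for the inclusion criteria. Section H's statement about multimorbidity concerns two or more conditions. It therefore keeps people with one condition and does nothing for people with none. Section 11 says CPRD will extract the dataset. If the extract follows the first sentence of Section K, condition-free patients are never delivered, and no later analysis can bring them back.

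The first planned Aim A results, the prevalence of each of the 220 conditions and of multimorbidity by sex, age, ethnicity and deprivation, would then describe people who already have a condition. They would be reported for a population that Section N calls unselected. Because the excluded share can differ between groups, the ethnic comparison, a core aim, would rest on denominators cut by different amounts.

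**Working it through.** **The plan's own figure.** Section I uses n = Z²P(1−P)/d² with Z = 1.96, P = 0.272 and d = 0.002. This gives 3.8416 × 0.272 × 0.728 / 0.000004 = 190,174.6, which matches the stated 190,174; multiplying by 1.10 gives the stated 209,191. Section H's 9,209,834 × 0.272 = 2,505,075 also reproduces. Both calculations treat 27.2% as a prevalence among all eligible patients.

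**Effect of the clause on prevalence.** Let q be the share of eligible adults with at least one listed condition. It is not in the documents, so a range is shown. Nobody with a given condition, or with multimorbidity, is removed; only the denominator shrinks. Hence prevalence after the clause = P/q.

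**Effect on pairs of conditions.** For two independent conditions with prevalences a and b, P00 = (1−a)(1−b) is the share with neither. The clause removes 1−q from that cell, so the odds ratio of 1 becomes [P00 − (1−q)]/P00. For a = b = 0.10, P00 = 0.81; for a = b = 0.05, P00 = 0.9025.

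| q | 27.2% becomes | Odds ratio, two 10% conditions | Odds ratio, two 5% conditions | n for d = 0.002 |
|---|---|---|---|---|
| 0.5 | 54.4% | 0.38 | 0.45 | 238,241 |
| 0.6 | 45.3% | 0.51 | 0.56 | 238,009 |
| 0.7 | 38.9% | 0.63 | 0.67 | 228,176 |
| 0.8 | 34.0% | 0.75 | 0.78 | 215,514 |
| 0.9 | 30.2% | 0.88 | 0.89 | 202,533 |

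Every n is far below 3 million, so the issue is bias and not sample size.

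**Effect on group contrasts.** A prevalence ratio p1/p2 becomes (p1/q1)/(p2/q2), that is, the true ratio times q2/q1. As an illustration, let condition counts be Poisson with means 1.1 and 0.8. Multimorbidity is then 30.1% and 19.1% (ratio 1.57), with q1 = 1 − e^(−1.1) = 0.667 and q2 = 1 − e^(−0.8) = 0.551. Under the clause the figures are 45.1% and 34.7% (ratio 1.30).

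**Effect on onset.** A cohort member with no condition at entry meets the clause only if one is recorded later. People who stay condition-free contribute no time at risk, so a rate of multimorbidity onset in the registered population would have too small a denominator.

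**The case against.** The strongest reply is that one clause stands against most of the Protocol. Sections G, N, P and T, and Section K's second paragraph, all describe an unrestricted population, so the clause may be a slip that nobody would apply. That stands as far as it goes: the documents contradict themselves, and they do not show a settled decision to exclude condition-free people.

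A reader might infer more than the documents support:

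- *Every denominator and every at-risk set is affected.* The listed secondary outcomes (Section C) run from index condition to cluster and from cluster to death. Both start from people who already have a condition, so the clause removes no condition-free person from those risk sets.
- *Onset of a first condition is a planned result that is lost.* In Section H, the onset to be determined is that of multimorbidity. No listed outcome is first-condition onset.
- *The membership ratio is corrupted.* For given clusters, every disease's overall prevalence rises by the same 1/q, so each ratio is multiplied by q. The ranking across clusters, and so the assignment of diseases, does not change.
- *Conditions will generally look inversely related.* That holds for independent or weakly related pairs. Holding P00 at 0.81, a true odds ratio above about 1/0.877 = 1.14 (q = 0.9) or 1/0.383 = 2.61 (q = 0.5) stays above 1 and is only attenuated. The Protocol also does not say that the clustering works on pairwise odds ratios, and clustering only people with two or more conditions would condition on morbidity more strongly still.
- *Group differences vanish.* With q exactly proportional to prevalence a ratio would fall to 1, but nothing in the documents supports such values. Direction and size depend on how q differs between groups.

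Finally, 27.2% refers to 36 conditions on 1 January 2012, while q here concerns 220 conditions recorded over 2010 to 2020. Dividing one by the other mixes definitions, so the results are illustrations and not forecasts.

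**Conclusion.** The point holds as an internal contradiction in the definition of the study population, with a bias that is certain in direction if Section K's first sentence is applied. For any q below 1, the Aim A prevalences are overstated by 1/q and no longer match the all-eligible basis of the 27.2%. The size depends on q, which the documents do not supply: 30.2% at q = 0.9 and 54.4% at q = 0.5, in place of 27.2%. A longer condition list and a longer window push q upward, so the smaller inflations should not be discounted. Group prevalence ratios are multiplied by the inverse ratio of the groups' q values, pairwise associations are biased downward, and condition-free entrants are selected on a later event. The index-condition and mortality transitions, and the ranking of diseases across given clusters, are not undermined by this route. The matter should be settled before the data are extracted.

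**What to change.** Delete the condition requirement from the first sentence of Section K, or confine it to clustering or trajectory subsets that are named as such. State the same base population in Sections G, H, K and N: all acceptable, linkage-eligible registered patients aged 16 or over in the included English practices, with or without a listed condition. Say that this population is the denominator for all prevalences and for the onset of multimorbidity. If clustering is run only in people with two or more conditions, describe that as an analysis subset and not as a criterion for entering the study.

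The cost is a few sentences and a larger extract than the clause would yield. Section I already describes its roughly 3 million as acceptable patients, so the planned size need not change, and neither does the 190,174 calculation.
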